## 7. Study Design and Description

### 7.1 Study Design

This is a multi-center, randomized, open-label, phase II clinical trial to evaluate the efficacy and safety of aumolertinib plus apatinib vs. aumolertinib monotherapy as first-line treatment in subjects with epidermal growth factor receptor mutation-positive (*EGFR*m+) advanced NSCLC. Subjects who meet the eligibility criteria will be randomized to the aumolertinib + apatinib group (test group) or the aumolertinib monotherapy group (control group) in a 1:1 ratio. Subjects in the test group will receive oral administration of aumolertinib 110 mg and apatinib 250 mg once daily, and subjects in the control group will receive oral administration of aumolertinib 110 mg once daily, in order to compare the efficacy and safety of the two treatment regimens. The schematic overview of the study is shown in Figure 1.

[figure not shown]

**Figure 1. Schematic overview of the study**

### 7.2 Inclusion Criteria

A subject must meet all the following inclusion criteria in order to be enrolled in this study:

1. Age over 18 years.
2. An Eastern Cooperative Oncology Group (ECOG) performance status score of 0 or 1, with no worsening over the previous 2 weeks, and minimum expected

survival of 12 weeks.

3. Histological or cytological confirmed locally advanced or metastatic NSCLC (including patients relapsing after prior surgical treatment or with an initial diagnosis of stage IIIB/IV, according to the AJCC 8th edition lung cancer staging criteria).
4. The patients have not received any systemic therapy after a confirmed diagnosis of locally advanced or metastatic NSCLC. For a patient who has received local treatment, if the lesions within the scope of the local treatment are non-target lesions, the patient may participate in the study.
5. Patients who have previously received preoperative neoadjuvant chemotherapy, postoperative adjuvant chemotherapy and concurrent chemoradiotherapy should meet the conditions that they have completed treatment for more than 6 months (inclusive 6 months).
6. Tumor tissue sample, blood sample, pleural effusion, peritoneal effusion or cerebrospinal fluid sample is tested by the central lab and confirmed positive for an *EGFR*-sensitizing mutation (Including but not limited to exon 19 deletion, or exon 21L858R, G719A, L861Q, etc.).
7. According to RECIST 1.1, participants must have measurable target lesions examined by PET-CT or CT or MRI. Imaging evaluation of the tumor will be performed within 28 days prior to the first dose.
8. Patients with asymptomatic brain metastases or brain lesions whose condition is stable after radiotherapy and who have completed radiotherapy for more than 28 days (including 28 days) can be enrolled.
9. Women of childbearing age must take appropriate contraceptive measures from screening to 3 months after the end of the study treatment and should not breastfeed. Before administering the drugs, a negative pregnancy test or meeting one of the following criteria proving that there is no risk of pregnancy:
  - a) Post-menopause is defined as amenorrhea for at least 12 months after

discontinuation of all exogenous hormone replacement therapy at an age older than 50 years.

b) Women under the age of 50 may also be deemed to be post-menopausal if they have experienced amenorrhea for 12 or more months after discontinuation of all exogenous hormone therapy, and their luteinizing hormone (LH) and follicle-stimulating hormone (FSH) levels are within the laboratory reference range for post-menopause.

c) Having previously undergone irreversible sterilization, including hysterectomy, bilateral oophorectomy, or bilateral salpingectomy, but not including bilateral tubal ligation.

10. From screening to 3 months after the end of the study treatment, male patients should use barrier contraceptives (i.e. condoms).
11. Subjects are personally willing to take part and sign a written Informed Consent Form.

### **7.3 Exclusion Criteria**

#### **Exclusion Criteria:**

A subject will not be eligible for inclusion in this study if any of the following criteria apply:

1. Receipt of any of the following treatments:
  - a) Receipt of any *EGFR* tyrosine kinase inhibitor therapy in the past.
  - b) Receipt of any VEGF receptor tyrosine kinase inhibitor or other anti-angiogenic agents;
  - c) Receipt of any PD-1/PD-L1 inhibitor or other immune checkpoint inhibitor agents;
  - d) The patient underwent major surgery within 4 weeks before the first dose of the study drug.
  - e) Receipt of radiotherapy for more than 30% of the bone marrow or extensive radiotherapy within 4 weeks before the first dose of the study drug.

- f) Receipt of potent CYP3A4 inhibitors, inducers, or drugs with a narrow therapeutic window which are CYP3A4 sensitive substrates within 7 days before the first dose of the study drug.
2. Patients with symptomatic brain metastases.
  3. Patients with other driver gene mutation including *ALK/ROS1* fusions.
  4. Patients with other malignant tumors and requiring standard treatment or major surgery within 2 years after the first dose of the study treatment.
  5. At the beginning of study treatment, those with residual toxicity from prior treatment greater than CTCAE grade 1 that cannot be alleviated, with the exception of hair loss and grade 2 neurotoxicity from prior chemotherapy.
  6. Suspected active tuberculosis infection or acquired immunodeficiency syndrome antibody (Anti-HIV) positive, anti-treponema treponema antibody (TP-Ab) positive, Hepatitis B surface antigen (HBV-AG) positive, HBV DNA copy number > the upper limit of normal test unit and other serious active fungal, bacterial and/or viral infections.
  7. Severe gastrointestinal dysfunction that may affect drug intake, transport, or absorption, such as inability to take oral drugs, uncontrollable nausea or vomiting, extensive gastrointestinal resection history, untreated recurrent diarrhea, atrophic gastritis, untreated stomach diseases requiring long-term use of proton pump inhibitors, Crohn's disease, ulcerative colitis, etc.
  8. Hepatic encephalopathy, hepatorenal syndrome or cirrhosis.
  9. Abnormal coagulation function (APTT > 1.5×ULN or INR > 1.5), thrombolysis, anticoagulation or antiplatelet therapy, bleeding tendency or active bleeding (such as hemoptysis, gastrointestinal bleeding, etc.); Arterial/venous thrombotic events such as cerebrovascular accidents (including transient ischemic attacks), deep venous thrombosis, and pulmonary embolism occurred in the 6 months prior to study initiation.
  10. Patients with hypertension who cannot be reduced to the normal range by

antihypertensive medication (systolic blood pressure  $>140$  mmHg, diastolic blood pressure  $>90$  mmHg).

11. A wound or fracture that has not healed for a long time.
12. Urine routine indicates urinary protein  $\geq ++$ , or 24-hour urinary protein quantity  $> 1.0\text{g}$ .
13. Grade 3-4 cardiac insufficiency (NYHA criteria) or meet any of the following cardiac test results:

- a) Mean corrected QT interval (QTc) of  $>470$  msec from 3 resting electrocardiograms (ECG), using Fridericia's formula to conduct QT interval correction (QTcF).
- b) Various clinically significant, important abnormalities in rhythm, conduction, or ECG morphology in a resting ECG (such as complete left bundle branch block, 3rd degree atrioventricular block, 2nd degree atrioventricular block, and PR interval  $>250$  msec).
- c) Any factors that increase the risk of QTc prolongation or arrhythmic events, such as heart failure, hypokalemia, congenital long QT syndrome, a history of long QT syndrome or sudden unexplained death under 40 years of age in the immediate family, or any concomitant drugs prolonging the QT interval.
- d) Left ventricular ejection fraction (LVEF)  $\leq 50\%$

14. Insufficient bone marrow reserve or organ function, reaching the following laboratory limits:

- a) Absolute neutrophil count  $<1.5 \times 10^9/\text{L}$ .
- b) Platelet count  $<100 \times 10^9/\text{L}$ .
- c) Hemoglobin  $<90$  g/L ( $<9$  g/dL).
- d) If no demonstrable liver metastases, alanine aminotransferase  $>2.5$  times the ULN; in the presence of liver metastases, alanine aminotransferase  $>5 \times \text{ULN}$ .
- e) If no demonstrable liver metastases, aspartate aminotransferase  $>2.5 \times \text{ULN}$ ; in the presence of liver metastases, aspartate aminotransferase  $>5 \times \text{ULN}$ .

f) If no demonstrable liver metastases, total bilirubin  $>1.5 \times \text{ULN}$ ; in the presence of Gilbert's syndrome (unconjugated hyperbilirubinemia) or liver metastases, total bilirubin  $>3 \times \text{ULN}$ .

g) Creatinine  $>1.5 \times \text{ULN}$  and creatinine clearance  $<50 \text{ mL/min}$  (calculated by the CockcroftGault formula); confirmation of creatinine clearance is only required when creatinine  $>1.5 \times \text{ULN}$ .

h) Serum albumin (ALB)  $<28 \text{ g/L}$ .

15. History of interstitial lung disease, history of drug-induced interstitial lung disease, history of radiation pneumonitis requiring steroid therapy, or any evidence of clinically active interstitial lung disease.

16. History of hypersensitivity to any active or inactive ingredient of aumolertinib or to drugs with a similar chemical structure to or of the same class as aumolertinib; History of hypersensitivity to any active or inactive ingredient of apatinib or to drugs with a similar chemical structure to or of the same class as apatinib.

17. Any severe or uncontrolled ocular disease (especially severe dry eye syndrome, dry keratoconjunctivitis, severe exposure keratitis, or other disease that may increase epithelial damage) that, in the physician's judgment, may increase the subject's safety risk; Or eye abnormalities that require surgery or are expected to require surgery during the study period.

18. Patients whose compliance with the procedures and requirements of the study could be poor, as determined by an investigator. If the subject has a clear history of neurological or psychiatric disorders (including epilepsy or dementia), is currently suffering from mental disorders, etc., Patients in whom any conditions compromising patient safety or interfering with study assessments are present, as determined by an investigator.

#### **7.4 Randomization**

This is a randomized, controlled, open-label, multicenter clinical trial. In this trial, randomization will be done by stratified blocked randomization (block size: 4)

using Clinflash IRT (Clinflash Healthcare Technology (Jiaxing) Co. Ltd., Zhejiang, People's Republic of China). The subjects will be randomized in a 1:1 ratio to the aumolertinib + apatinib group or the aumolertinib monotherapy group with *EGFR* mutation status (exon 19 deletion *vs.* exon 21 L858R *vs.* atypical mutations) and metastatic site (CNS metastasis *vs.* no CNS metastasis) at enrollment as stratification factors.

Eligible subjects will be assigned a unique randomization number on the day of the first dose of the investigational medicinal product (the first day of the first treatment cycle, C1D1). The investigator will assign a randomization number and medication number to all screened eligible subjects who qualify for the study after randomization.

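### The open-label protocol prints one fixed block size of 4; the foresight this gives is modest because about 20 sites share the blocks, but it is cheap to remove

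*Protocol*

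**What the plan says.** Protocol section 7.4 (Randomization) contains all the relevant statements:

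- Blinding: "This is a randomized, controlled, open-label, multicenter clinical trial".
- Method: "randomization will be done by stratified blocked randomization (block size: 4", run "using Clinflash IRT".
- Ratio: "The subjects will be randomized in a 1:1 ratio".
- Strata: three classes of EGFR mutation (19del, L858R, atypical), crossed with presence or absence of CNS disease, which the section words as "metastatic site (CNS metastasis *vs.* no CNS metastasis) at enrollment as stratification factors". That makes 3 × 2 = 6 strata. Site is not listed.
- Issue of numbers: on the day of first dose, and "The investigator will assign a randomization number and medication number to all screened eligible subjects who qualify for the study after randomization".

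The synopsis plans about 98 patients at about 20 sites. Sections 5 and 9.1.2 base the endpoints, including PFS, on investigator assessment under RECIST 1.1.

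**The concern.** In an open-label trial each site learns its own past allocations. If the block length is also known and never varies, those past allocations carry information about the next one. An investigator who expects a particular arm can hold back a patient, bring one forward, or lean on a judgement-based criterion. Section 7.2 asks for a minimum expected survival of 12 weeks, and section 7.3 lets the investigator exclude for expected poor compliance. Selection of that kind is not repaired by the analysis. The trial is also small: one patient is 1/49, or about 2 percentage points, of an arm's rate.

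This is not a gap that a statistical analysis plan could fill. The protocol itself gives the block size to everyone who holds it.

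**Working it through.** **Inputs from the protocol.** Block size 4, ratio 1:1, six strata without site, open-label (section 7.4); about 98 patients and about 20 sites (synopsis).

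**Step 1: what a full view of a stratum gives.** A 2:2 block of 4 has six equally likely orders.

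- Certain in advance: the fourth allocation always; the third when the first two match, which is 2 of 6 orders. Share certain = (1 + 1/3)/4 = 33.3%.
- Correct guesses when always choosing the arm with more places left: 1/2, 2/3, 2/3 and 1 at positions one to four. Mean = (17/6)/4 = 17/24 = 70.8%.
- In a simulation of 98 patients over six strata, allowing for unfinished blocks, about 31% of allocations are certain to such an observer.

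**Step 2: what one site sees.** On average 98/20 = 4.9 patients per site, spread over six strata, or 4.9/6 = 0.8 per stratum. Most of each block is filled elsewhere.

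The simulation uses blocks shared across sites and an investigator who sees only own-site allocations and guesses the under-represented arm. The protocol gives neither stratum prevalences nor enrolment shares, so these are assumptions: 19del/L858R/atypical 50/40/10%, CNS metastasis 30%, and the shares shown.

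| Situation | Correct guesses at that site |
|---|---|
| Chance | 50% |
| 20 equal sites (5% each) | about 51% |
| Site enrolling 30% | about 54% |
| Site enrolling 50% | about 56% |
| Site enrolling 80% | about 60 to 61% |
| One site enrolling everyone | about 70% |
| 20 equal sites, blocks also cut by site (not stated) | about 57% |

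**Step 3: what varying the size gains.** With block ends known, size 6 gives 25.0% certain and 68.3% guessed. An even mix of 4 and 6 gives (4 × 70.8% + 6 × 68.3%)/10 = 69.3%, an upper limit because sizes and block ends would not be known. In simulation, simple guessing with full sight falls from about 70% to 68%. At single sites the change is at most about half a point. The main gain is therefore not a lower average guess rate: an observer can no longer be sure where most blocks end.

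**Step 4: what it costs in balance.** Within a stratum, a block of 4 limits the difference between arms to 2 and a block of 6 to 3. Over six strata the theoretical worst case moves from 6 × 2 = 12 to 6 × 3 = 18.

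**The case against.** The strongest reply is that blocks are shared by about 20 sites, so an ordinary investigator is close to coin-tossing, and that short fixed blocks are a reasonable way to keep six strata balanced in 98 patients. Both parts stand. They set the size of the point and rule out a stronger reading: a reader might infer that upcoming allocations can generally be foreseen. That needs someone who sees nearly all allocations in a stratum, and the protocol gives no investigator such a view. The one-third figure describes that observer and not the typical site.

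A reader might also infer that section 7.4 contradicts itself, because an IRT performs the randomization while "The investigator will assign a randomization number and medication number to all screened eligible subjects". The rest of that sentence places this step after randomization and limits it to eligible subjects. Read in order, the IRT randomizes and the investigator then passes on the numbers. Nothing says that the investigator holds or generates the list. The wording is loose, but no breach of concealment follows from it.

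Finally, unblinded reading of progression is a separate source of bias. It comes from the open-label design and would be the same under any block size.

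What the reply does not provide is a reason to print the block size. Balance can be kept with short blocks of varying, undisclosed length.

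**Conclusion.** The point holds as a minor, avoidable weakness. The protocol discloses a single fixed block size in an open-label trial. The resulting foresight is about 1 percentage point above chance at an ordinary site, and about 4 to 10 points at a site enrolling 30% to 80% of patients. It becomes material only if one site dominates enrolment, if sites share allocations, or if blocks are in fact cut by site.

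The one-third and 70.8% figures are exact but apply only with full sight of a stratum. The site figures rest on the assumed prevalences and shares above, and on reading the listed strata as complete. The sentence on who assigns the numbers needs clarification only and is not a finding by itself.

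**What to change.** - Remove the block size from section 7.4. Say only that stratified permuted blocks are used, with details in a restricted randomization specification held away from sites.
- For blocks not yet issued, use randomly varying sizes, for example 4 and 6. Blocks already issued stay as they are.
- As clarification, state that the IRT issues the randomization and medication numbers once eligibility is confirmed and that the investigator receives them. Confirm also that blocks are not cut by site.

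The cost is a new IRT list for the remaining blocks, a few wording edits, and slightly larger possible imbalance in small strata (at most 3 instead of 2 within a stratum). The sample size does not change. If the list can no longer be altered, the wording changes are still worth making.

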## **8. Study Procedures**

Each subject will be assessed by the same investigator or study site personnel when possible at each step.

The subject must read and voluntarily sign the ICF approved by the site's ethics committee prior to the initiation of any study procedures. All study procedures should be performed within the time windows indicated in the schedule of activities. See Appendix A for the overall follow-up schedule.

### **8.1 Screening Period**

Inpatient or outpatient subjects will be screened after signing the informed consent form and undergo relevant laboratory tests and assessments. Subjects who meet all the inclusion criteria and do not meet any of the exclusion criteria may be enrolled.

### **8.2 Treatment Period**

All eligible subjects will be randomized in a 1:1 ratio to the following 2 groups:

#### **1) Aumolertinib + apatinib group:**

Aumolertinib: strength: 55 mg/tablet; dose: 110 mg/day (2 tablets/day), p.o. QD;

Apatinib: strength: 250 mg/tablet; dose: 250 mg/day (1 tablet/day), p.o. QD.

2) Aumolertinib monotherapy group:

Aumolertinib: strength: 55 mg/tablet; dose: 110 mg/day (2 tablets/day), p.o. QD;

Each treatment cycle consists of 21 days of continuous administration. After treatment is started, efficacy will be evaluated once every 6 weeks ( $\pm 7$  days) as per RECIST 1.1. Subjects will continue treatment until progressive disease assessed by investigator per RECIST 1.1 or until the withdrawal or discontinuation criteria are met. Subjects may continue to receive the treatment even if progressive disease per RECIST 1.1 occurs as long as they still benefit from the treatment as judged by investigator; if it is decided to continue the treatment, the baseline and follow-up plan will not be affected by the additional courses of treatment. Once the treatment is discontinued due to lack of clinical benefit upon judgment, it cannot be started again.

### **8.3 Follow-up Period**

Subjects who discontinue the treatment due to meeting the discontinuation criteria should complete the treatment discontinuation follow-up, the 30 days safety follow-up after treatment discontinuation, and survival follow-up once every 12 weeks ( $\pm 7$  days) as specified in the study plan.

Subjects without progressive disease at treatment discontinuation will be followed up once every 6 weeks ( $\pm 7$  days) until progressive disease assessed by investigator per RECIST 1.1 (both intracranial and systemic), even if the subject has received other anti-tumor treatments; after progressive disease, the subjects will be followed up for survival once every 12 weeks as specified in the study plan.

## **9. Endpoint Evaluation and Statistical Analysis**

### **9.1 Anti-Tumor Activity Evaluation**

#### **9.1.1 Investigator Assessment as per RECIST 1.1**

At each visit, the investigator will assess the subject's tumor response according to RECIST 1.1 by comparing with baseline and previous assessments, depending on subject's status. The progression of target lesion (TL) will be calculated by comparing

with tumor burden at its nadir (i.e., the smallest sum of previously recorded diameters). In the absence of progression, tumor response and stable disease (SD) will be calculated by comparing with baseline tumor measurements obtained prior to the start of the treatment. For subjects with indeterminable tumor status, if there is evidence of progression, they will be considered to have progressive disease (PD); if there is no evidence of progression, they will be considered not evaluable (NE). The endpoints of this study will be analyzed based on the tumor response assessment by the investigator per RECIST 1.1, and the investigator will also manage subjects only based on the assessment results.

The investigator will evaluate the response to treatment using RECIST 1.1 by determining the ORR, DCR, DoR, and progression-free survival (PFS). In addition to the overall tumor imaging evaluation performed by the investigator as per RECIST 1.1, for extracranial and/or intracranial lesions (no more than 5 target lesions in the whole body) selected for overall evaluation, the respective intracranial and extracranial response evaluation (ORR, DCR, DOR) will be performed according to the response evaluation criteria in RECIST 1.1, and the investigator does not need to select additional lesions.

#### **9.1.2 18-month Progression-free Survival (PFS) Rate**

PFS is defined as the time from randomization to the first time of disease progression (assessed by RECIST v1.1) or death, whichever occurred earlier, evaluated by investigators. Patients with treatment discontinuation for any reason will be censored at the date of the last progression assessment with no documented progression. PFS-derived data are based on assessment date rather than visit date.

#### **9.1.3 Overall survival (OS)**

OS is defined as the time from the date of the first dose to the date of the subject's death due to any cause. A subject who has not died at the time of statistical analysis will be censored at the time point when the subject is last known to be alive.

#### **9.1.4 Confirmed Objective Response Rate (ORR)**

As per RECIST 1.1, confirmed ORR is defined as the percentage of subjects with complete response (CR) or partial response (PR) lasting for at least 2 times evaluation before PD.

Data until PD or last evaluable data in the absence of PD will be recorded in the assessment of ORR. However, any CR or PR that occurs after discontinuation of the study treatment and further anti-tumor treatment will not be included in the calculation of ORR.

Table 2 provides the criteria used to determine objective tumor response of TLs.

